### Blood sampling and biomarker measurements

Blood sampling and biomarker analysis are some of the main goals and hypotheses of this study. Up to 50 ml of blood per study visit (t0, t2, t3, t4) will be sampled. Blood collection (serum, plasma, RNA out of PAXgene tubes), processing, and storage will be performed according to local established standard operating procedures (SOPs). Serum and plasma will be briefly kept at 4 °C until processing. Serum will be stored for 45 minutes for coagulation. Serum and EDTA-plasma will be centrifugated for 10 minutes at 2,000 x g and stored as 500µl aliquots at − 80 °C. The cellular pellet from the EDTA-tube will be reconstituted in PBS and stored at –80 °C for DNA extraction. The PAXgene tube will be stored for 120 minutes at room temperature, followed by 24 hours at − 20 °C and long-term storage at − 80 °C until use.

The investigation is initially designed as a prospective single sample survey and longitudinal data collection. With the help of various protein-analytical or other measurement methods, new biomarkers for POD, cognitive decline, and dementia will be identified and validated. In addition to proteomic or metabolomic markers, genomic and epigenetic markers, such as the ApoE genotype, will be examined. The participants are therefore explicitly advised that a genetic examination of the donated material may be carried out. To protect the participants, no feedback is given about individually achieved markers, in particular predictive markers. To test our hypothesis that pre-surgical AD pathology is a risk factor to develop POD followed by cognitive decline, we will measure plasma Aβ using our recently developed two-step immunoassay [58, 59], p-tau181 [60, 61], NfL [62, 63], and GFAP [26] using SIMOA technology [64, 65].

Samples will be handled according to our recently published SOP suggestions to minimize pre-analytical effects on plasma Aβ [66]. As POD and cognitive decline are often considered to be associated with a concomitant increase in inflammatory cytokines, we want to identify markers that correlate with delirium and neurodegenerative markers. Therefore, we will also analyze a cytokine panel, including IL-1ra-, IL-6, IL-8, IL-10, and tumor necrosis factor (TNF) alpha [23, 67–69]. Furthermore, to overall understand the impact of specific cardiovascular alteration and to test the hypothesis that changes in cardiovascular markers are associated with delirium, we will analyze the cardiovascular marker growth differentiation factor 15 (GDF-15) [70].

### Study sample

In order to plan a subsequent confirmatory study, it is necessary to estimate the necessary parameters with sufficient accuracy. The sample size planning is specifically based on estimating the area under the curve (AUC) of the delirium risk assessment for the occurrence of delirium with a 95% confidence interval so that the 95% confidence interval has a width of approximately 0.05 points. It is assumed that the prevalence of POD is 50% and that there is a true AUC of 0.7. If 416 patients are analyzed, the 95% confidence interval extends approximately 0.025 points from the estimate. To compensate for possible dropouts (assumed dropout rate approx. 20%), 500 patients will be recruited. The calculation was done in nQuery 8.

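### The planned precision of the primary AUC is overstated twofold: 416 patients give a 95% confidence interval of about ±0.05, not ±0.025

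*Protocol article*

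**What the plan says.** The Study sample section of the protocol article bases the sample size on how precisely the AUC of the delirium risk assessment can be estimated, with a view to planning a later confirmatory study. The number of patients is chosen "so that the 95% confidence interval has a width of approximately 0.05 points". The inputs are given in one sentence: "It is assumed that the prevalence of POD is 50% and that there is a true AUC of 0.7". The resulting claim is "If 416 patients are analyzed, the 95% confidence interval extends approximately 0.025 points from the estimate". The recruitment target follows: "To compensate for possible dropouts (assumed dropout rate approx. 20%), 500 patients will be recruited". On method, the section says only "The calculation was done in nQuery 8"; it does not name a variance formula.

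**The concern.** An AUC of 0.7 estimated from about 200 patients per outcome group normally has a standard error of about 0.025. A 95% interval should then reach about twice that distance from the estimate. The article gives 0.025 as the whole distance.

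The two precision statements agree with each other (2 × 0.025 = 0.05), so the text cannot be rescued by reading its 0.05 as a half-width.

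This figure is the only precision the study promises and the only quantitative justification for its size. It concerns the primary aim, validating the risk assessment. A confirmatory study planned on the stated figure would take the uncertainty in its main input to be half of what it is.

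**Working it through.** **Inputs, all from the Study sample section.** True AUC A = 0.7; prevalence 50%; 416 analysed, hence n1 = 208 with delirium and n0 = 208 without; two-sided 95% interval (multiplier 1.96). Stated result: half-width 0.025, full width 0.05.

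**Formula (assumed, since the article names none).** Hanley-McNeil standard error of a single AUC:

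SE = √{[A(1−A) + (n1−1)(Q1−A²) + (n0−1)(Q2−A²)] / (n1·n0)}, with Q1 = A/(2−A) and Q2 = 2A²/(1+A).

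**Numbers.**
- Q1 = 0.7/1.3 = 0.5385, so Q1 − 0.49 = 0.0485
- Q2 = 0.98/1.7 = 0.5765, so Q2 − 0.49 = 0.0865
- Variance = [0.21 + 207 × 0.0485 + 207 × 0.0865] / (208 × 208) = 0.000650
- SE = 0.0255
- Half-width = 1.96 × 0.0255 = 0.0500; full width = 0.100

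**Can the article's figures be reproduced?** The sample size can; the precision cannot. The Hanley-McNeil half-width is 0.0501 with 414 patients and 0.0500 (just under 0.05) with 416. So 416 is the smallest even number that meets a half-width of 0.05. A half-width of 0.025 needs 1,660, about four times as many, as expected when the width is halved.

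**Other methods, same inputs, 416 analysed.**

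| Method | Half-width | Full width |
|---|---|---|
| Hanley-McNeil | 0.0500 | 0.100 |
| Obuchowski binormal variance | 0.0518 | 0.104 |
| Exact Mann-Whitney variance, equal-variance binormal model | 0.0497 | 0.0995 |
| Logit-scale interval (0.648 to 0.748) | – | 0.0997 |
| Simulation, 5,000 replicates (SE 0.0252) | 0.049 | – |

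**Other readings that might yield 0.025 (Hanley-McNeil unless noted).**
- One-sided 95% bound: 0.042
- 80% interval: 0.033
- 416 patients in each outcome group: 0.035
- All 500 recruited patients analysed: 0.046
- Simple binomial variance, 1.96 × √(0.21/416): 0.044

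None comes close. At 416 patients, a half-width of 0.025 would require a true AUC of about 0.94.

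**Sensitivity to the plan's other assumptions.** If 20% of the 500 recruited are lost, 400 remain and the half-width is 0.051. Equal outcome groups are a favourable case: at 21.4% delirium, the rate the Background cites for patients aged 65 or over, the half-width at 416 is 0.061 to 0.066 depending on the formula.

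**The case against.** The strongest objection is that the variance formula and the values entered in the software are not shown, so Hanley-McNeil is an assumption, and the exact match at 416 holds only under it. With the Obuchowski variance, 448 patients would be needed for a half-width of 0.05. That caveat is fair, but it does not help the stated figure: every standard method tried gives 0.049 to 0.052. Nor can a rounding word such as approximately cover a factor of two.

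Second, the cause cannot be settled. The value 0.05 may have been entered as the distance to the limit and later described as the full width, or the standard error, which rounds to nearly the same 0.025, may have been reported as the half-width. The match at 416 favours the first, but the article does not show it. The correction is the same either way.

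Third, the article states a target width of 0.05 outright, so one could argue that the sample size is wrong and the wording right. This stands as a question for the investigators. Since 416 follows from a half-width of 0.05, the wording is the likelier slip.

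Finally, this is an observational study with no hypothesis test or power claim resting on the figure, and the reported interval will show the true precision. That limits the harm. It does not make the stated basis for the sample size correct.

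**Conclusion.** The stated precision is wrong as written. Under the article's own inputs (AUC 0.7, equal outcome groups, 416 analysed), the 95% interval extends about 0.050 from the estimate, with a plausible range of 0.049 to 0.052 across formulas. That is twice the distance claimed. The conclusion rests on the article's AUC, prevalence and number analysed, and on a standard large-sample variance for a single AUC; it does not depend on which of those variances is chosen. It must be corrected because it is the sole stated basis for the sample size of the primary aim.

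**What to change.** Keep the sample size and replace the precision statements with wording such as: With 416 analysed patients, a true AUC of 0.7 and 50% prevalence, the 95% confidence interval extends approximately 0.05 from the estimate (total width approximately 0.10). Change the target sentence to match, name the variance formula used, and carry ±0.05 into the planning of the confirmatory study. The cost is a text correction and a less favourable stated precision; no patients are added.

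If the investigators do require a total width of 0.05, the sample size has to change instead: about 1,660 analysed patients by Hanley-McNeil, or 1,786 by the Obuchowski variance. With 20% dropout, 1,660 analysed means 1,660/0.8 = 2,075 recruited, against the 500 planned.

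### Recruiting 500 leaves 400 patients at the stated 20% dropout, not the 416 required; 500 covers dropout only up to 16.8%

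*Protocol article*

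**What the plan says.** The Study sample section of the protocol article plans for precision of an estimated AUC, assuming a delirium prevalence of 50% and a true AUC of 0.7. The number to be analysed appears in this sentence: "If 416 patients are analyzed, the 95% confidence interval extends approximately 0.025 points from the estimate". The step from analysed to recruited patients follows: "To compensate for possible dropouts (assumed dropout rate approx. 20%), 500 patients will be recruited".

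The total of 500 is repeated in the Abstract, in Study setting and participants, and in the Discussion. The article gives no inflation formula, no other dropout rate and no rule for replacing patients who drop out.

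**The concern.** The section gives three linked numbers: 416 to be analysed, about 20% lost, and 500 recruited to make up for the loss. If 20% of those recruited are lost, 500 does not yield 416. The recruitment target then misses the section's own analysis target under its own assumption.

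What is at stake is mainly whether the calculation is correct and can be reused. The section says that the study is meant to supply parameters for planning a later confirmatory study, so others may carry this calculation forward. The loss of information from this step alone is slight.

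**Working it through.** **Inputs, all from the Study sample section.** Analysed N = 416; dropout d = 0.20 (stated as approximate); recruited N = 500; AUC = 0.7; prevalence 50%; 95% confidence.

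**1. Reproducing the plan's 500.**
- Dividing by the retained fraction: N / (1 − d) = 416 / 0.80 = 520. This does not give 500.
- Adding 20% of the analysed number: N × (1 + d) = 416 × 1.2 = 499.2, rounded up to 500. This gives the printed figure.
- Equivalently, the margin is 500 − 416 = 84 patients. That is 84/416 = 20.2% of the analysed number, but 84/500 = 16.8% of those recruited.

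**2. What 500 delivers at 20% dropout.** 500 × (1 − 0.20) = 400. The shortfall is 416 − 400 = 16 patients, and 16/416 = 3.8%.

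**3. Dropout that 500 can absorb.** 1 − 416/500 = 0.168, or 16.8%.

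| Dropout | Analysed from 500 | Recruits needed for 416 |
|---|---|---|
| 16.8% | 416 | 500 |
| 18% | 410 | 508 |
| 19% | 405 | 514 |
| 20% | 400 | 520 |

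**4. Effect on precision.** The standard error of the AUC scales very nearly with 1/√N, so the interval widens by √(416/400) = 1.020, about 2%. This ratio holds whatever half-width is taken for 416.

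As a check by the Hanley-McNeil variance, put A = 0.7, Q₁ = A/(2 − A) = 0.5385, Q₂ = 2A²/(1 + A) = 0.5765, and n patients in each group. Then SE² = [A(1 − A) + (n − 1)(Q₁ − A²) + (n − 1)(Q₂ − A²)] / n².
- n = 208 (total 416): SE = 0.0255, half-width 1.96 × 0.0255 = 0.0500.
- n = 200 (total 400): SE = 0.0260, half-width 1.96 × 0.0260 = 0.0510.

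The difference is 0.001. The half-width of 0.0500 at 416 does not match the printed 0.025. That is a separate issue in the same section; it is not used here beyond the relative change.

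**The case against.** The strongest defence is that the dropout rate is given only as approximate, and that all three figures agree at 16.8%. Delirium is also assessed within the first five postoperative days, so losses for that outcome could prove lower than planned. This has some force: it is too strong to say that the three numbers can never hold together. But 16.8% is a stretched reading of about 20%. At 19% or 18%, 500 still leaves only 405 or 410. The sentence offers 500 as compensation for the stated rate, and at that rate it falls short.

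A second defence is that the effect is trivial. That stands as to size. The calculation targets interval width, so no hypothesis test or power figure is lost.

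Three stronger readings are tempting, and the documents do not support them.
- A reader might infer that the investigators certainly multiplied by 1.2. The match with 499.2 makes this likely, but no formula is shown, and rounding to a convenient 500 is also possible.
- A reader might infer that the shortfall seriously damages precision, particularly if delirium is less common than the assumed 50%. Any marked widening in that case would come almost wholly from the changed prevalence, not from the 16 patients.
- A reader might infer that recruiting 520 would secure the stated interval width. It would restore 416 analysed patients and no more; whether 416 gives that width is the separate issue noted above.

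**Conclusion.** The point holds as a small, definite arithmetic error. At the stated 20% dropout, 500 recruits give 400 analysable patients, 16 (3.8%) below the required 416. Full compensation needs 520, and 500 is enough only up to 16.8%. The cost in precision is an interval about 2% wider.

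The conclusion takes 416 as given, reads dropout as a share of those recruited, and takes the approximate rate at its stated value. It does not depend on how 500 was obtained.

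**What to change.** Keep 500 and correct the one sentence in the Study sample section. Either of these would do:
- *Recruiting 500 patients allows for a dropout rate of up to about 17%* (exactly 16.8% if 416 must be met in full).
- *With a dropout rate of 20%, about 400 of the 500 recruited patients are expected for analysis.*

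The first stands on its own. If the second is used and a half-width is added for 400 patients, it must be calculated on the same basis as the half-width for 416, and the two corrected together where necessary. Placing 0.051 for 400 beside the printed 0.025 for 416 would create a new contradiction.

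The cost is one sentence, with no additional patients and no change to the design or analysis.

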### Statistical analysis

Prognostic quality measures are calculated in order to determine the prognostic properties of continuous endpoints and delirium risk assessment scores in predicting the development of POD, postoperative cognitive decline, and AD. Specifically, a receiver operating characteristics (ROC) analyses is conducted for each of the outcomes and the associated area under the curve (AUC) is reported with optimal cut-off points (simultaneous maximization of sensitivity and specificity, as well as according to Youden). Furthermore, sensitivity, specificity, positive and negative predictive values ​​for the optimal cut-off point are reported. The observed incidence risk factors for the development of POD, cognitive decline, AD, or Lewy body dementia will be investigated using logistic regression or, in the case of time-to-event data, cox regression. Effect sizes are reported as odds ratio or hazard ratio. As far as possible, all key figures are given with a 95% confidence interval. In addition to the univariate consideration of the individual parameters, a multivariate consideration of predictive factors is also planned. For this purpose, machine learning methods for supervised learning are employed (e.g. multivariate logistic regression) and candidate models are trained on a training data set (70% of the data collected). Different models and their corresponding accuracy are compared using a test data set (30% of the data collected). The division of data into test and training data set is random.

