While there are well-established predictors for delirium incidence, a standardized screening assessment for the risk of POD is not available [33–35]. Lindroth et al. [31] examined numerous assessments for delirium prediction. Overall, the American College of Surgeons (ACS) National Surgical Quality Improvement Program risk calculation for serious complication (NSQIP-SC) and the Trail Making Test B (TMTB), a measure of executive function, have been shown to predict POD severity using advanced modeling techniques [31]. However, further research is needed to establish a reliable and time-efficient screening instrument for delirium in the preoperative daily routine of cardiac surgery.

Our primary aim is to validate an existing delirium risk assessment in context of cardiac surgery. This delirium risk assessment was previously developed in the multicenter, cluster-randomized PAWEL study [36] and incorporates information from the medical record, patient report, and brief bedside cognitive testing that can be performed preoperatively. Secondary aims are i) to identify specific preoperative and perioperative factors associated with delirium, cognitive decline, and accelerated dementia after cardiac surgery, and ii) to identify blood-based biomarkers that predict the incidence of postoperative delirium, cognitive decline, or dementia in the context of cardiac surgery.

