### Preoperative screening (t0)

Upon admission, preoperative delirium risk will be assessed using a questionnaire (Additional file 1: Supplement 1) adapted from the multicenter, cluster-randomized PAWEL study [36]. This delirium risk assessment will be validated in context of cardiac surgery. This preoperative risk assessment questionnaire includes the following assessments: A) Geriatric check (mobility, statutory level of independency, cognition, psychological symptoms, and previous hospital stay); B) Short 6-item cognitive screening; C) General information including results from A) and B), age > 80, laboratory measurement (e.g., increased creatine, CRP, hemoglobin, decreased protein), and an American Society of Anesthesiologists (ASA) score ≥ 3 [37]. The patient's current medications are also noted; however, particular attention is paid to the number of medications and medications with a deliriogenic risk. Furthermore, preoperative diagnosis of depression, stroke, dementia, and previous hospital stays within the last year will be assessed. Additionally, the patient’s level of care and whether the patient is a nursing home resident will be assessed. Study participants will be asked about previous delirium and a recent increase in number of falls. Another component of the survey is the self-reported subjective memory impairment (SMI), alcohol use, and smoking status. Finally, the patient's handgrip strength will be measured by the Jamar® Hydraulic Hand Dynamometer.

Furthermore, basic sociodemographic information will be collected, including marital status, number of children, immigrant background, level of education, occupation, living arrangement, and care level. Moreover, an examination of previous cardiac and noncardiac comorbidities will be provided (Additional file 2: Supplement 2). Frailty will be assessed using the 7-point Clinical Frailty Scale of the Canadian Study of Health and Aging (CSHA Frailty Scale, 1-very fit up to 7-severely frail) [38]. In addition, the outcome-oriented nursing assessment instrument AcuteCare 1.1 (ePA-AC) [39], whereby the software generates a delirium risk score and a self-care score, will be assessed from the MEONA software. Factors biasing the adequate elicitation of the ePA-AC (Additional file 3: Supplement 3), such as the understaffing of nurses, will be documented.

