The primary aim of our study is to analyze the reliability, sensitivity, and specificity of an existing delirium risk assessment in context of cardiac surgery. Secondary aims are i) to identify specific preoperative risk factors and perioperative exposition factors for POD, cognitive decline, and accelerated dementia after cardiac surgery, and ii) to identify serum biomarkers that predict the incidence of POD, cognitive decline, or dementia in the context of cardiac surgery.

Our FINDERI study design has several strengths. The longitudinal study design with two year follow up has the potential to identify patients with cognitive dysfunction or accelerated dementia after cardiac surgery. In addition, the study utilizes the highest standards for delirium detection, including the CAM, CAM-ICU, and chart review. Finally, the study analyzes a broad and representative population in cardiac surgery. However, this study has several limitations. Firstly, we will focus our primary and secondary hypotheses on identifying pre- and perioperative delirium risk factors, and not on the impact of delirium on morbidity, mortality, and hospital utilization of patients undergoing cardiac surgery or its treatment. Secondly, if study participants decline an in-hospital follow up study visit (e.g., due to a high risk of COVID-19 infection), we will not be able to measure a blood sample. Third, further research will be needed to replicate our findings in a larger multicenter, prospective, observational study.

From the clinical perspective, this study might help to identify patients at high risk for delirium, and to develop interventions to prevent delirium prior to cardiac surgery. Furthermore, this study might help to identify important biological mechanisms by which surgery is associated with delirium. Finally, the identification of specific blood biomarkers might help to predict delirium, cognitive decline, and dementia in patients undergoing cardiac surgery.

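### Sensitivity, specificity and predictive values are read at a cut-off tuned on the same patients, so they are modestly optimistic; the AUC is unaffected.

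*Protocol article*

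**What the plan says.** The Background section gives the aim: "Our primary aim is to validate an existing delirium risk assessment in context of cardiac surgery". The Discussion words the same aim as being "to analyze the reliability, sensitivity, and specificity of an existing delirium risk assessment in context of cardiac surgery". The tool is a questionnaire "adapted from the multicenter, cluster-randomized PAWEL study" (Preoperative screening section). The article states no cut-off for it.

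The Statistical analysis section plans a ROC analysis for each outcome, covering delirium, cognitive decline and Alzheimer's disease, and applies it to the risk scores and to continuous measures. The AUC "is reported with optimal cut-off points (simultaneous maximization of sensitivity and specificity, as well as according to Youden". Sensitivity, specificity and both predictive values "for the optimal cut-off point are reported".

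The same section describes a random split in which "candidate models are trained on a training data set (70% of the data collected" and compared on the remaining 30%. That split is introduced for the multivariable models only.

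**The concern.** Validating an existing tool normally means applying it as it stands to new patients and reporting how it performs. Here the threshold measures are read at a point on the ROC curve chosen because it performed best in these patients. A maximum picked from noisy values is too high on average. An interval that treats the chosen cut-off as given also ignores the search.

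The Study sample section says the estimates are meant to support planning of a confirmatory study. The Discussion links identification of at-risk patients to prevention programmes and closer screening, which is a threshold decision. Optimistic accuracy, or a cut-off that would move in a second sample, would carry into both.

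**Working it through.** **The plan's own figure.** The plan gives no figure for the threshold measures. Its only precision figure concerns the AUC: "It is assumed that the prevalence of POD is 50% and that there is a true AUC of 0.7", and "If 416 patients are analyzed, the 95% confidence interval extends approximately 0.025 points from the estimate". As a check, the Hanley-McNeil variance with 208 cases and 208 non-cases is [A(1−A) + 207(Q₁−A²) + 207(Q₂−A²)] / (208 × 208), where Q₁ = A/(2−A) = 0.538 and Q₂ = 2A²/(1+A) = 0.576. This gives SE = 0.0255 and a half-width of 1.96 × 0.0255 = 0.050, not 0.025. That mismatch is a separate matter. Only the AUC, the prevalence and N are used below.

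**Inputs.** From the Study sample section: AUC 0.70, N = 416, prevalence 50%. From the Background section, as alternative prevalences: 21.4% (age 65 or over) and 33.5% (over 80). Assumed: an equal-variance binormal score and, for discrete scores, evenly spaced levels. The article does not show the tool's score range.

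**Method.**
1. Scores are N(0,1) without delirium and N(d,1) with delirium, where d = √2 × Φ⁻¹(0.70) = 0.742.
2. The best attainable Youden index (J = sensitivity + specificity − 1) is 2Φ(d/2) − 1 = 0.289.
3. In each simulated study of 416 patients (3,000 to 4,000 runs per setting), the cut-off c that maximises J is chosen.
4. Apparent accuracy at c is compared with the truth at the same c: sensitivity 1 − Φ(c − d), specificity Φ(c).

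**Results.**

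| Score | Prevalence | Apparent J | True J at chosen cut-off | Excess | 95% CI coverage, sensitivity | SD of true sensitivity |
|---|---|---|---|---|---|---|
| Continuous | 50% | 0.320 | 0.280 | 0.040 | 0.909 | 0.09 |
| Continuous | 33.5% | 0.322 | 0.279 | 0.043 | 0.911 | 0.10 |
| Continuous | 21.4% | 0.328 | 0.277 | 0.051 | 0.895 | 0.11 |
| 12 levels | 50% | 0.297 | 0.278 | 0.019 | 0.948 | 0.11 |
| 12 levels | 21.4% | 0.301 | 0.276 | 0.025 | 0.946 | 0.12 |
| 6 levels | 50% | 0.286 | 0.286 | 0.000 | 0.951 | 0.02 |
| 6 levels | 21.4% | 0.286 | 0.285 | 0.001 | 0.959 | 0.04 |

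Coverage uses Wilson intervals, except simple Wald intervals for 6 levels. Wald coverage for the continuous score is 0.889 (50%) and 0.864 (21.4%).

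**By measure, continuous score (apparent vs true).**
- At 50%: sensitivity 0.667 vs 0.645, specificity 0.654 vs 0.635, PPV 0.664 vs 0.644, NPV 0.668 vs 0.647.
- At 21.4%: sensitivity 0.673 vs 0.632, specificity 0.655 vs 0.646, PPV 0.356 vs 0.335, NPV 0.883 vs 0.869.

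**Comparison with sampling error.** At a fixed cut-off with sensitivity 0.645, the 95% half-width is 1.96 × √(0.645 × 0.355 / 208) = 0.065 with 208 cases, and about 0.10 with 89 cases (0.214 × 416). The bias is smaller than this.

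**Rarer outcomes.** The article gives no rate for late outcomes. If 10% or 5% of 416 patients had the event (assumed), the excess in J for a continuous score would be 0.07 or 0.11.

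**Two criteria.** The first criterion is not defined by a formula. Taking it as closest to the perfect corner of the ROC plot, which is one possible reading, it and Youden select different cut-offs in more than half of runs for a continuous score and in about a third for 12 levels. The mean absolute difference in sensitivity over all runs is 0.05 to 0.07.

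**The case against.** **The tool is probably coarse.** It is built from items and flags, so a discrete score is the natural reading. For 12 levels or fewer, interval coverage is nominal and the bias in sensitivity is about 1 to 2 points. This stands, and it limits the size of the point for the primary tool. It does not remove the instability at 12 levels, and the continuous figures still apply to the biomarkers, which are secondary.

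**The AUC is sound.** The study is sized on the AUC, which needs no cut-off. This stands. A reader might infer that the tool will not be validated at all, or that a new threshold is being tested in place of an existing one. The documents do not support either reading: discrimination of the score is assessed properly, and no threshold for the adapted tool is shown that could be displaced.

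**Two criteria do not mean selective reporting.** A reader might suspect that the more favourable cut-off will be reported. The text speaks of cut-off points in the plural, by one criterion as well as the other, which suggests that both are given. The later singular leaves open only which one the accuracy measures refer to.

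**Interval methods belong in the analysis plan.** The article promises 95% intervals as far as possible and does not say how they are built, so it cannot be faulted for using naive ones. The coverage figures show only what would happen if the search were ignored.

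**The study is preparatory.** It precedes a confirmatory study and states that replication is needed. This softens the consequence, but the estimates are meant to inform that study.

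**Conclusion.** The point holds in limited form. Reading accuracy at a cut-off optimised in the same patients is a stated rule, not an omission; it touches quantities that the Discussion places in the primary aim, and the hold-out split does not reach it. Sensitivity, specificity, PPV and NPV will be optimistic to a modest degree: in sensitivity plus specificity, about 0.04 to 0.05 for a continuous score, 0.02 to 0.03 for 12 levels, and close to zero for 6. The weightier issue for continuous and 12-level scores is that the chosen cut-off would vary from study to study, with an SD of true sensitivity of about 0.09 to 0.12. These sizes rest on the assumed binormal score, AUC 0.70, 416 analysed patients and evenly spaced levels.

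**What to change.** 1. If the adapted tool has a cut-off, fix it before outcomes are seen and report the main sensitivity, specificity, PPV and NPV there. Selection bias is then zero by construction.
2. If it has none, label the reported cut-off as newly derived in this study.
3. For every data-derived cut-off, including those for continuous markers, state which single criterion (for example Youden) the accuracy measures refer to.
4. At those cut-offs, give optimism-corrected sensitivity, specificity, PPV and NPV, with intervals from a bootstrap that repeats the cut-off search in each resample.

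A bootstrap is preferable to extending the 70/30 split to this analysis. At 50% prevalence the test part would hold about 0.3 × 208 = 62 cases, with a half-width for sensitivity of about 0.12 against 0.065 in the full sample.

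The cost is a few lines in the analysis plan, a little more programming and slightly less favourable accuracy figures. No further patients or data are needed.
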